### 7.4.2 Documentation and Reporting Obligations: INVESTIGATOR

Serious Adverse Events have to be documented on the SAE-forms and the investigator must report them to the sponsor immediately. If more information about the SAE becomes available later, it must also be reported to the sponsor immediately. Serious adverse events (SAE) will be documented for patients in both treatment arms (VPA and LEV) **starting at the moment of initiating the infusion of IMPs. All SAEs will be documented until the end of the study** (Visit 2).

The Serious Adverse Events that are also endpoints are to be reported as described in chapter 7.1.3.

In the event of a patient's death, the investigator/ the deputy or the authorised medical staff provide the leading ethics committee(s), all involved ethics committees in multi-centred trials, the responsible federal authority and the sponsor with all further information needed to fulfil their tasks **upon request**.

In all the reports, personal data are to be pseudonymized by using the patient's identification code. It must be possible to relate the initial and all follow-up reports to each other by means of the patient identification number, name and address or the like.

The investigator, the deputy or the authorised medical staff must report every Serious Adverse Event as soon as it is known to the following address:

**ZKS Leipzig / Arzneimittelsicherheit**  
Universität Leipzig

 In general, hospitalisation means that the patient stays (usually at least an overnight stay) at the hospital or emergency ward for observation and/or treatment. Complications that occur during the stay are AEs. If a complication prolongs hospitalisation or fulfills any other serious criteria, the event is serious.

Hospitalisation for elective treatment of a pre-existing condition that did not worsen from baseline is not considered an AE.

Zentrum für Klinische Studien Leipzig  
[name]  
Telefon: [name]  

### **7.4.3 Documentation and Reporting Obligations: SPONSOR**

After the ZKS Leipzig receives the SAE, it is immediately passed on to the coordinating investigator/responsible person for medical assessment.

The coordinating investigator/responsible person forms a second medical opinion of the SAE with respect to causal relationships and the decision as to whether or not it was expected, as described in chapter 16.1.3 and 16.1.4 and forwards the second opinion to the ZKS Leipzig within two days of its arrival.

In the ZKS Leipzig the SAE data are entered into the SAE database immediately and the MedDRA coding takes place simultaneously.

Then forwarding as per law and as described in Chapter 7.6 only for Suspected Unexpected Serious Adverse Drug Reactions (SUSARs) takes place.

Details of the sponsor's documentation and reporting obligations will be specified in a special, trial-specific pharmacovigilance plan, which will be written and finalised alongside with this protocol, if possible.

## **7.5 Periodic Reports**

### **7.5.1 Annual Safety Report**

According to German Medicinal Products Act the sponsor writes a safety report annually (Annual Safety Report, ASR^2) and sends this report to the leading ethics committee and the federal authority.

Should there be additional regular reports (Periodic Safety Reports – PSR) required by ethics committee and/or authority according to the approval statement, these will also be provided by the sponsor.

The key date is the date of the first authorization of the clinical trial by a federal authority. All data obtained up to this date (each year) will be included in the ASR. Beginning with the key date, there is a time-limit of 60 days for the preparation and submission of the ASR.

The ASR will be prepared by the ZKS Leipzig (project manager, responsible biometrician and PV data manager) acc. to the national requirements Deadlines regarding the ASR are based on the German Medicinal Products Act.

The final report will be released in co-operation with the principal investigator/sponsor's representative.

---

 See "Detailed guidance on the collection, verification and presentation of adverse reaction reports arising from clinical trials on medicinal products for human use").

## 7.6 Suspected Unexpected Serious Adverse Reactions (SUSAR)

### 7.6.1 Definition

Suspected Unexpected Serious Adverse Drug Reactions (SUSARs) are side-effects (there is at least a reasonable possibility for a relationship between the Adverse Event and the administration of the investigational product, i.e., the relationship cannot be ruled out), the nature or severity of which are inconsistent with the information available about the product. Information about the trial products are contained in the SmPCs (Summary of medicinal Product Characteristics).

### 7.6.2 Documentation und Reporting Obligations

#### Information for SPONSOR

The sponsor submits all information available about a SUSAR immediately to the leading ethics committee, the responsible federal authority, and to all participating primary investigators, at the latest within 15 calendar days after the event becomes known.

For every SUSAR that results in death or a life-threatening condition, the leading ethics committee, the federal authority and all participating investigators must be informed by the sponsor within 7 calendar days after the event becomes known. Additional information has to be given within 8 further calendar days.

Details of the sponsor's documentation and reporting obligations will be specified in a special, trial-specific pharmacovigilance plan which will be written and finalised alongside with this protocol, if possible.

#### Information for INVESTIGATOR

The investigator passes down all relevant information concerning the SUSAR to all participating trial investigators at his/her trial centre. This has to be confirmed by the investigator by signing an acknowledgement document.

To ensure that the investigators and all other trial personell remain "blind" in the case of a SUSAR, the investigating centres will receive all potential SUSARs without information concerning the administered drug (i.e. regardless of whether the patient was treated with LEV or VPA).

## 7.7 Other Safety Relevant Issues

Other safety issues also qualify for expedited reporting where they might materially alter the current benefit-risk assessment of an investigational medicinal product or would be sufficient to consider changes in the investigational medicinal products administration or in the overall conduct of the trial, for instance:

New events related to the conduct of a trial or the development of an IMP likely to affect the safety of subjects, such as:

- a serious adverse event which could be associated with the trial procedures and which could modify the conduct of the trial,
- a significant hazard to the subject population such as lack of efficacy of an IMP used for the treatment of a life-threatening disease,
- a major safety finding from a newly completed animal study (such as carcinogenicity),
- a temporary halt of a trial for safety reasons if the trial is conducted with the same investigational medicinal products in another country by the same sponsor
- Recommendations of the DMC, if any, where relevant for the safety of subjects.

The sponsor, together with the DMC if appropriate, decides if the number of events or qualitative changes in the expected SARs comprise a safety issue and must be reported.

## 7.8 Therapeutic Procedures.

If a patient requires treatment as a result of an Adverse Event, then it must meet the recognized standards of medical care in order to restore the patient's health. Appropriate resuscitation devices and medication must be available in order to treat the patient as quickly as possible in the event of an emergency.

The action taken to treat the AE/SAE must be documented by the investigator either in the appropriate CRF and/or using additional documents.

## 7.9 Dealing with Pregnancy

Regarding the planned study population pregnancies are not expected events in the course of the trial.

# 8 BIOMETRY

## 8.1 Biometrical Aspects of the Trial Design

### 8.1.1 Measures to Prevent Bias

#### Randomisation

Randomisation in a 1:1 ratio is performed as block randomisation with randomly varying block length stratified by centre.

#### Randomisation procedure

Randomisation lists are created by statistical software. Blocks of randomly chosen length are created as realisations of random samples and stringed together to a list.

ZKS Leipzig delivers one randomisation list per centre each to the central pharmacy Erlangen. Beginning with the first entry in the randomisation list, the staff of the pharmacy packs medication kits for one patient each. Every kit is labelled by a consecutive ID number and contains a sealed opaque envelope revealing the information about the medication. A pre-defined number of kits are packed into a package and are sent to the trial sites. The medical personal in the trial sites is obliged to take the set with the lowest ID number. Treatment failure is defined as clinical evidence of epileptic activity and / or persistent electroencephalographical ictal activity consistent with NCSE according to the Salzburg criteria 15 minutes after the initiation of intervention or recurrence of ictal activity (in case of NCSE return of EEG patterns to baseline status after initial treatment response) during the further 45 minutes observing period which leads to immediate unblinding of medication. In case of treatment success, drug therapy will be unblinded after 60 minutes to ensure appropriate further treatment (see Figure 1). The investigator is responsible that the envelope is not opened before.

Every trial site is equipped first with a start package of fixed number of medication sets. The size of further packages may be adapted in accordance to the accrual of the trial sites.

The trial sites inform the ZKS about every included patient and transfer the medication ID. Matching the randomisation list with the correspondent list from the central pharmacy Erlangen, the ZKS is able to oversee the randomisation process and the medication logistics.

By study design most of the effects in secondary endpoints cannot be unequivocally attributed to the trial medication. Regarding the parameters, they are not susceptible to biased evaluation either. To minimize bias arising from evaluation of EEG-patterns, EEG evaluation trainings shall be performed. Each trial site will be equipped with working instructions to ensure homogeneity of procedures. These working instructions will cover:

1. The preparation of the intervention
2. The procedures during 60 minutes after the start of intervention
3. The procedure of uploading the EEG data
4. The report of AEs.

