**patients with**

confusion/ fluctuating mental state **and** (minimal) rhythmic motor activity (as twitching of the arms, legs, trunk or facial muscles, blinking, tonic eye deviation or nystagmoid eye jerking) **or**

comatose/stuporous state **and** (minimal) rhythmic motor activity (see above)

Clinically defined diagnosis of NCSE is only permitted if EEG is not available or justified for verification of NCSE. In particular, clinical NCSE must not be diagnosed if NSCE is suspected, but EEG is ambiguous.

2. Adult patients  $\geq 65$  years old
3. Written informed consent by patient. Due to the nature of the disease, informed consent cannot be obtained at the time of inclusion in the trial (see chapter 4.3).

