## 6.5 Plan for Further Treatment

Beyond the single infusion the treatment of SE is determined by the responsible clinicians and follows clinical standards. The possible further treatment with one of the trial drugs VPA or LEV will be observed according to the study design.

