## 8.2 End Points

### 8.2.1 Primary End Point

Primary endpoint is the effectiveness of intravenous valproate (VPA) or levetiracetam (LEV) to terminate eSE and maintain control of epileptic activity **up to 60 minutes** after initiation of the trial intervention defined:

- ⇒ for patients with CSE: cessation of convulsions within 15 min after initiation of infusion, subsequent stable cessation of convulsions during 60 minutes after initiation of infusion.
- ⇒ for patients with NCSE: cessation of EEG signs of NCSE according to Salzburg criteria (Leitinger et al. 2016) within 15 min after initiation of infusion, subsequent stable cessation of ictal EEG activity according to the Salzburg criteria during 60 minutes after initiation of infusion as evaluated by the external EEG reference board.

Evaluation of this endpoint is possible for each patient.

Statistically, the time to cessation as well as the success rate is evaluated.

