#### Efficacy

- Time from initiation of trial intervention to cessation of eSE within 60 minutes
- Neurological status (including vigilance) 60 minutes after initiation of intervention

- Difference of blood levels of VPA and LEV before and 60 minutes after initiation of intervention
- Recurrence of seizures or nonconvulsive/ convulsive SE after initially successful intervention
- For patients who failed the primary endpoint, number of patients in whom SE ceased during 60 minutes after initiation of intervention according to the treating physician
- For NCSE patients who failed the primary endpoint, time to first cessation, as verified by EEG
- Number of patients with SE-associated ventilation until hospital discharge
- Functional outcome at discharge, defined by Barthel Index (BI) and modified Rankin Scale (mRS)

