#### Safety

- Mortality
- Need for any emergency medication (different from allocated study drug) during 60 minutes after initiation of study intervention
- Need for ventilation (noninvasive/ invasive) during 60 minutes after initiation of intervention
- ~~Number of patients with SE-associated ventilation until hospital discharge~~
- Intrahospital complications
  - Incidence of delirium as diagnosed by the treating physician
  - Infections requiring intravenous administration of anti-infectives
  - Adverse events related to infusion/subsequent therapy with antiepileptic drug (sedation, dizziness, nausea, vomiting, thrombocytopenia, leukopenia, hypotension, new elevation of liver enzymes, hyperammonaemia, acute new liver failure or pancreatic damage, tremor, psychiatric abnormalities)

The mRS is the recommended outcome measure in stroke trials as it is directly relevant to the patient's ability to return to daily life. Its scores range from 0 (no impairment) to 6 (death) and include special items as walking and independence that are indicative of the degree to which a patient is competent to participate in daily activities (Lees et al. 2012). As most of the seizures occurring in elder people are caused by an underlying structural brain injury the clinical phenomenology of focal convulsive SE or nonconvulsive SE may imitate stroke-related deficits. Thus, the effects on functional outcome may be quantified meaningfully and appropriately by the mRS. The Barthel Index is also a well-established clinicometric scale which is utilized to reflect elderly patient's need for care in particular and includes basic activities such as transfer and personal hygiene (Mahoney and Barthel 1965).

The secondary endpoints will provide valuable insights into the disorder in this age group. There is a special emphasis on characteristics of SE and concomitant intrahospital complications to provide an equal evaluation of the efficacy and safety of antiepileptic treatment in the elderly.

The combination and comparison of the retrospective and prospective assessment of mRS and BI are chosen in order to quantify its consequences on functional outcome.

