#### Determination of primary and secondary measures

All clinical scales (GCS, mRS, BI) are validated and widely used in clinical settings and / or clinical trials. They will be performed by trained neurologists. The pre-mRS and pre-BI reflect the functional status of the patient before the admission to the hospital and will be scored by the patient or a close relative if the patient's capability is impaired. Recurrence of SE or seizures during the hospital stay is defined as witnessed convulsions with or without

impairment of consciousness in case of CSE and the detection of ictal EEG activity in case of NCSE. SE-associated mortality includes all cases of death during the hospital stay even if they are not directly related to SE. The necessity to invasive ventilation is defined as the proportion of patients who have to be ventilated during the hospital stay.

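### In convulsive SE, the treatment-failure rule in 8.1.1 is wider than the primary-endpoint bullet in 8.2.1, so some patients unblinded as failures can be read as primary successes

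*Protocol*

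**What the plan says.** **Failure rule.** Section 8.1.1 (Randomisation procedure) reads "Treatment failure is defined as clinical evidence of epileptic activity and / or persistent electroencephalographical ictal activity consistent with NCSE", by the Salzburg criteria, 15 minutes after the infusion starts. Recurrence of ictal activity in the following 45 minutes also counts. Failure leads to immediate unblinding, and the rule is not split by type of status epilepticus (SE).

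**Primary endpoint.** The lead sentence of 8.2.1 describes the endpoint as the ability of the drug "to terminate eSE and maintain control of epileptic activity" up to 60 minutes. The bullet that makes this operational for convulsive SE is narrower: "for patients with CSE: cessation of convulsions within 15 min after initiation of infusion, subsequent stable cessation of convulsions" up to 60 minutes. The NCSE bullet uses the Salzburg criteria as read by the external EEG board.

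**Site checks.** At T15, and from T15 to T60, section 6.3 tells sites to look for convulsive seizures, minimal rhythmic motor activity, or EEG signs of NCSE by the Salzburg criteria. Between T15 and T60, any recurrence of ictal activity triggers unblinding. The physician may then wait, repeat the infusion or give another drug. Section 6.5 adds: "Beyond the single infusion the treatment of SE is determined by the responsible clinicians and follows clinical standards".

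**Rescue.** Section 8.2.2 lists as a safety endpoint "Need for any emergency medication (different from allocated study drug) during 60 minutes after initiation of study intervention". Section 8.2.1 does not mention rescue or early unblinding.

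**NCSE recurrence.** In 8.1.1 it is described as a return of the EEG pattern to its baseline state after an initial response. Sections 6.3 and 8.2.1 use the Salzburg criteria.

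**The concern.** Clinical evidence of epileptic activity is a wider class than convulsions, and the protocol itself names signs that lie between the two. In the definition of clinically diagnosed NCSE, section 4.1 lists "minimal) rhythmic motor activity (as twitching of the arms, legs, trunk or facial muscles, blinking, tonic eye deviation or nystagmoid eye jerking". Section 6.3 lists minimal rhythmic motor activity separately from convulsive seizures. A CSE patient whose convulsions stop but who keeps such a sign is a failure under one section and can be called a success under another.

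This concerns the primary endpoint. The trial may already have declared such a patient a failure, opened the envelope and given a second treatment. If the literal bullet is then applied, control maintained with that second treatment would be credited to the randomised drug. One secondary endpoint inherits the ambiguity, because its denominator is the set of primary failures: "For patients who failed the primary endpoint, number of patients in whom SE ceased during 60 minutes after initiation of intervention".

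The NCSE mismatch is a separate and smaller matter. Two sites looking at the same EEG could unblind, and change treatment, at different times.

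**Working it through.** **1. The plan's own figure.** Inputs from 8.3.1 and 8.4: success rates 60% and 47%, two-sided 5% level, 80% power, 1:1 allocation. With the unpooled two-proportion formula,

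n per arm = (1.960 + 0.8416)² × (0.60 × 0.40 + 0.47 × 0.53) / 0.13² = 7.849 × 0.4891 / 0.0169 = 227.15,

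or 454.3 in total, against the stated 454. The sample size reproduces and is not in question.

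**2. The CSE rules side by side.**

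| CSE patient | 8.1.1 | 8.2.1 bullet, read literally | 8.2.1 lead sentence |
|---|---|---|---|
| Still convulsing at 15 min | Failure | Failure | Failure |
| Convulsions stopped, other clinical ictal sign present at 15 min | Failure, unblinded | Success if convulsions stay away to 60 min | Failure |
| Free of signs at 15 min, non-convulsive ictal sign recurs before 60 min | Failure, unblinded | Success | Failure |
| No ictal sign to 60 min | Success | Success | Success |

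The two middle rows are in dispute. The EEG half of the 8.1.1 rule plays no part in this, because the schedule of assessments plans trial EEG only for NCSE patients.

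**3. Rescue.** In the middle rows, unblinding opens the way to further treatment under 6.3 and 6.5. Because 8.2.1 has no clause on rescue, the literal bullet would still call the patient a success if convulsions did not return.

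**4. Scale.** 454 / 2 = 227 per arm. One patient scored the other way moves that arm's rate by 1/227 = 0.44 percentage points. Planned successes are 227 × 0.60 = 136.2 and 227 × 0.47 = 106.7, a difference of 29.5 patients. The protocol does not say how many CSE patients fall in the middle rows, so the calculation stops here.

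**5. NCSE recurrence.** Suppose Salzburg-positive activity returns in a form that differs from the entry EEG. Under 6.3 the site unblinds. Under 8.1.1, if baseline means the original pattern, this is not a recurrence and the envelope stays closed to 60 minutes. Under 8.2.1 the patient is a primary failure in either case, since the board applies the Salzburg criteria.

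**The case against.** **The disputed CSE patient is rare.** Section 4.1 counts focal convulsive seizures as CSE, so continued rhythmic twitching of a limb or the face may already mean that convulsions have not stopped. That narrows the group, mainly to eye and blink signs, but does not empty it.

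**Each term belongs to one entry category.** On this reading, minimal rhythmic motor activity in 6.3 is meant only for clinically defined NCSE, and 8.1.1 is shorthand for the same split. This is possible, but 8.1.1 does not say so. Even its clinical half, applied to CSE alone, is wider than convulsions.

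**The lead sentence of 8.2.1 settles it as failure.** It does point that way. A reader might infer that such patients will be scored as successes; the text does not support that. It supports only that two sentences disagree and nothing ranks them.

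**The narrow wording is deliberate.** A reader might cite 8.2.2, where "Recurrence of SE or seizures during the hospital stay is defined as witnessed convulsions" for CSE. That sentence concerns a later secondary endpoint and says little about control between 15 and 60 minutes.

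**Rescue cannot create a success.** For a patient still convulsing at 15 minutes this is right: a later drug cannot produce cessation within 15 minutes. It does not cover the middle rows of the table.

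**The SAP, the site instructions or Figure 1 may resolve it.** None of these is available here. Derivation details may well belong in an SAP, but conflicting protocol text should not be left for an unseen document to reconcile, and sites act on the protocol when they unblind.

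**Baseline means a Salzburg-positive EEG.** For patients entered on EEG that is a fair reading, and on it the NCSE mismatch is only loose wording.

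**Conclusion.** The concern holds in limited form. In CSE the protocol gives two incompatible answers to who is a primary-endpoint failure, for patients whose convulsions have stopped but who show other clinical ictal signs up to 60 minutes. The conclusion rests on reading convulsions as narrower than clinical evidence of epileptic activity, which the separate listing in 6.3 supports.

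The affected group is probably small. A reader might infer a loss of power or a bias between arms; neither is shown, because the documents give no frequency for these patients and no reason to expect more of them in one arm. A reader might also infer that the NCSE primary result is affected. It is not: 8.2.1 and the EEG board govern it, and the baseline wording in 8.1.1 bears only on when sites unblind.

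The point deserves correction because it touches the definition of the primary endpoint and the remedy is inexpensive.

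**What to change.** 1. In the CSE bullet of 8.2.1 write: *cessation of convulsions and of any other clinical evidence of epileptic activity, including minimal rhythmic motor activity, within 15 min and stable to 60 min*.
2. Add to 8.2.1, for CSE only: *a patient unblinded for treatment failure, or given a further antiseizure drug for ongoing or recurrent SE before 60 min, is a primary-endpoint failure*.
3. In 8.1.1 replace the wording on return of the EEG to baseline with recurrence of ictal EEG activity according to the Salzburg criteria, and refer to 8.2.1 for the definition of failure.

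The rule in item 2 should not extend to NCSE. There it would let a site decision override the blinded board, which is a different and debatable design choice.

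The cost is one wording amendment and the matching site working instruction. No new assessment or data item is needed: 6.3 already has sites check for minimal rhythmic motor activity, 5.6 records the time and reason of unblinding, and 7.1.3 records emergency medication within 60 minutes. A repeat infusion of the same drug falls outside that medication item, but the unblinding record captures the recurrence before it. The downside is that CSE success rates may be slightly lower than under the literal bullet.

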### 2.2 Secondary Objectives

Secondary goals are to assess the safety profile of VPA and LEV in elderly patients with eSE, and to collect observational data about eSE.

Therefore, the following points will be evaluated:

- Time from initiation of intervention to cessation of eSE within 60 minutes
- Neurological status (including vigilance) 60 minutes after initiation of infusion
- Difference of blood levels of VPA and LEV before and 60 minutes after initiation of intervention
- Recurrence of seizures or nonconvulsive/ convulsive SE after initially successful intervention
- For patients who failed the primary endpoint, number of patients in whom SE ceased during 60 minutes after initiation of intervention according to the treating physician
- For NCSE patients who failed the primary endpoint, time to first cessation, as verified by EEG
- Number of patients with SE-associated ventilation until hospital discharge
- Functional outcome at discharge, defined by Barthel Index (BI) and modified Rankin Scale (mRS)
- Mortality
- Need for any emergency medication (different from allocated study drug) during 60 minutes after initiation of study intervention
- Need for ventilation (noninvasive/ invasive) during 60 minutes after initiation of intervention
- Intrahospital complications
  - Incidence of delirium as diagnosed by the treating physician
  - Infections requiring intravenous administration of anti-infectives

Adverse events possibly related to infusion/subsequent therapy with antiepileptic drug (sedation, dizziness, nausea, vomiting, thrombocytopenia, leukopenia, hypotension, new elevation of liver enzymes, hyperammonaemia, acute new liver failure or pancreatic damage, tremor, psychiatric abnormalities).

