**Visit 2 (V2)****Day of discharge/day before discharge from hospital or day 30 (+/- 1 day), whatever is sooner**

- Record the following data (eCRF)
  - day of recurrence of seizures or convulsive SE after successful intervention/ day of detection of NCSE (EEG) after successful intervention
  - day of first EEG-detection of terminated NCSE after failed intervention
  - further antiepileptic treatment after intervention: medication, dosage, type and frequency of application including stop of medications
  - reason for withdrawal of treatment with VPA or LEV
  - acute renal failure with or without dialysis
  - acute pancreatitis
  - acute hepatic failure
  - lab analysis: level of ammoniaemia and subsequent repetitions, as ordered by treating physician \*
  - type of infections requiring i.v. antibiotic treatment
  - start and stop of invasive/noninvasive ventilation (day)
  - development of delirium and treatment
  - complications requiring surgery or invasive diagnostics/ therapy
  - etiology of SE (cerebral focus, metabolic/infectious/toxic conditions, noncompliance/withdrawal/change of antiepileptic medication)
  - home care after hospital stay (if applicable)
- Administer GCS and perform brief neurological exam: orientation, horizontal extraocular movements, motor drift of both arms and legs, sensation, language.
- Obtain mRS and BI

\* **NOTE:** As soon as an otherwise unexplained disturbance of consciousness, nausea or hypotension occurs in duration of treatment with VPA during the hospital stay the efforts of clarification **must** include the detection of a potential hyperammonemia.

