#### Blinding

Patients as well as treating physicians are blinded until 60 min after initiation of the infusion at the latest. After 60 minutes at the latest, the medication is unblinded in order to be able to decide on further treatment.

For unbiased evaluation of the primary endpoint final EEG is assessed by two expert raters (EEG reference board) blinded to treatment arm allocation.

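### Section 8.1.1 declares the secondary endpoints free of evaluation bias, which is wrong for the physician-judged endpoints, the relatedness-filtered adverse events and hyperammonaemia

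*Protocol*

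**What the plan says.** Section 8.1.1, on measures to prevent bias, states about the secondary endpoints: "Regarding the parameters, they are not susceptible to biased evaluation either".

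The other relevant provisions are these.

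- **Unblinding.** Section 8.1.1 (Blinding): "After 60 minutes at the latest, the medication is unblinded in order to be able to decide on further treatment". For failures it comes earlier: ictal activity at 15 minutes, or its recurrence "during the further 45 minutes observing period which leads to immediate unblinding of medication".
- **Blinded assessment.** It is provided for the EEG: "For unbiased evaluation of the primary endpoint final EEG is assessed by two expert raters (EEG reference board) blinded to treatment arm allocation". No other endpoint has it.
- **Physician-judged endpoints.** Section 8.2.2 lists "Incidence of delirium as diagnosed by the treating physician", and its adverse-event item includes sedation, dizziness and psychiatric abnormalities. Follow-up runs to discharge or day 30 (3.4).
- **Relatedness.** Section 8.2.2 counts "Adverse events related to infusion/subsequent therapy with antiepileptic drug"; section 2.2 has "Adverse events possibly related to infusion/subsequent therapy with antiepileptic drug" for the same list. Causality is assessed at the site (16.1.3).
- **Ammonia.** Hyperammonaemia is in the 8.2.2 list for both arms. Ammonia is absent from the blood tests at screening (6.2.1), at T60 (6.3) and in the schedule of assessments. Under Visit 2 it is recorded if the treating physician ordered it. A note there makes the work-up compulsory when "an otherwise unexplained disturbance of consciousness, nausea or hypotension occurs in duration of treatment with VPA during the hospital stay the efforts of clarification" are under way. There is no counterpart for levetiracetam (LEV).

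**The concern.** The sentence in 8.1.1 is the protocol's stated reason for having no safeguard on the secondary endpoints. If it is wrong, a reader of the results will take arm differences in delirium, sedation or hyperammonaemia as if they had been assessed blind and looked for equally.

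Safety carries weight in this trial. Section 1.2.1 says that superior efficacy of one drug, possibly VPA, might be offset by a better safety profile of LEV, and 8.5.2 foresees chi-squared or mid-p comparisons of event rates. Unequal search for hyperammonaemia would count against VPA, the direction in which that offset would be argued. For judgements made with knowledge of the drug the direction is open: section 5.5.2 associates sedation, agitation and delirium with LEV, and hyperammonaemia and liver abnormalities with VPA, so the assessor knows what to expect in either arm.

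**Working it through.** **1. The passages side by side**

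| Endpoint | When and by whom judged | Open to evaluation bias? |
|---|---|---|
| Mortality | all deaths in the hospital stay, whatever the cause (8.2.2) | no |
| Emergency medication, ventilation within 60 min | blinded until failure or 60 min | partly |
| Blood count, liver enzymes at screening and T60 | scheduled in both arms | little or none |
| All (S)AEs | recorded in both arms (7.1.3), rates reported (synopsis) | less |
| SE ceased within 60 min per treating physician, in failures | envelope may already be open | partly |
| Delirium, sedation, dizziness, psychiatric abnormalities | site staff, mostly after unblinding | yes |
| Listed AEs if *related* | causality judged by site staff, mostly after unblinding | yes |
| Hyperammonaemia | work-up compulsory during VPA treatment only | yes, through detection |

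The last three rows contradict the sentence in 8.1.1. In addition, the T60 examination has a window of +/- 5 minutes (6.3) while unblinding is due by 60 minutes. No text fixes which comes first, so the 60-minute neurological status may be assessed with the envelope open.

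**2. Numbers per arm**

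The protocol plans 454 evaluable patients (8.4). With 60% vs 47%, two-sided 5%, power 80% and unpooled variance:

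(1.960 + 0.842)² × (0.60×0.40 + 0.47×0.53) / 0.13² = 7.849 × 0.4891 / 0.0169 = 227.15 per arm, or 454.3 in total.

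The figure reproduces, and 227 per arm is used below.

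**3. Unequal detection of hyperammonaemia**

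Let t be the true incidence, equal in both arms, and d_V and d_L the shares of cases detected. The observed rates are t·d_V and t·d_L, so the observed risk ratio is d_V/d_L although the true one is 1. The chance of a significant result is the sum, over all pairs (x, y), of Bin(x; 227, t·d_V) × Bin(y; 227, t·d_L) wherever the uncorrected chi-squared test rejects at 5%.

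The documents give neither t nor d. All values here are assumptions.

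| d_V vs d_L | Observed RR | t = 5% | t = 10% | t = 20% |
|---|---|---|---|---|
| equal | 1.0 | about 5% | about 5% | about 5% |
| 30% vs 20% | 1.5 | 7% | 10% | 16% |
| 40% vs 20% | 2.0 | 13% | 24% | 43% |
| 90% vs 60% | 1.5 | 13% | 23% | 44% |
| 40% vs 5% | 8.0 | 44% | 76% | 98% |

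In counts, for the last row at t = 10%: 227 × 0.10 × 0.40 = 9.1 and 227 × 0.10 × 0.05 = 1.1 expected detected cases. Nine vs one in 227 each gives chi-squared p = 0.0105 (Fisher p = 0.020) with no true difference.

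**4. Relatedness filter**

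Take equal adverse-event rates of 10%, 20% or 30% in both arms, called related in 70% of cases in one arm and 50% in the other (also assumed). The observed risk ratio is 0.70/0.50 = 1.4. The chance of a false difference, by the normal approximation to the same test, is 14%, 26% or 38%.

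**The case against.** The strongest counter-case has five parts.

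- **Scope.** A reader might infer that the whole safety comparison is biased, or that only related events are counted. The protocol does not support either. The filter sits in one item of 8.2.2; 7.1.3 documents all adverse events in both arms and captures the listed complications separately without it, and the synopsis reports (S)AE rates. Delirium and infections are not filtered, and infections are defined in working instructions. This stands and limits the point to the endpoints marked above.
- **The filter is weak.** Under 16.1.3 a reasonable possibility includes events that other causes could explain and events that cannot be judged. This narrows the gap between *related* and *possibly related*. It does not remove the two wordings or the unblinded judgement.
- **The ammonia rule follows current treatment, not randomised arm.** The protocol assumes 53% failure on LEV (100% − 47%). Some of those patients may receive VPA and come under the rule, and VPA-arm patients taken off VPA leave it. This reduces the imbalance by an unknown amount. It would vanish only if VPA exposure after the infusion were similar in both arms, which nothing in the protocol ensures.
- **Size.** No testing rates are documented, and equal true incidence is itself doubtful, since 5.5.2 names hyperammonaemia for VPA and not for LEV. That is correct. If VPA truly causes more, the observed risk ratio is the true one multiplied by d_V/d_L, so unequal detection exaggerates a difference instead of creating it.
- **Status.** Section 8.4 calls the secondary analysis mainly explorative, and the offset in 1.2.1 is rationale, not a decision rule. This stands: no confirmatory test is damaged.

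Section 8.1.1 also concedes that most secondary effects cannot be clearly attributed to the trial drug, and unblinding for further treatment is deliberate. Both are reasonable, but neither addresses who judges the event or how hard it is looked for.

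**Conclusion.** The statement in 8.1.1 is wrong for part of the secondary endpoints and should be corrected. Three weaknesses follow from the protocol's own text: unblinded judgement of delirium, sedation, dizziness, psychiatric abnormalities and causality; one adverse-event endpoint defined in two ways, with a filter that 7.1.3 does not use; and a hyperammonaemia endpoint with a compulsory work-up under one drug only. A direction is evident only for hyperammonaemia, where detection is likely higher in the VPA arm.

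The size cannot be stated. Over the assumed detection shares, and with equal true incidence of 5% to 20%, the chance of a false significant difference runs from about 7% (30% vs 20%) to about 98% (40% vs 5%). These figures show sensitivity and are not a forecast.

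It does not follow that the safety comparison as a whole is biased. The primary endpoint lies outside this point; mortality, scheduled laboratory values and overall (S)AE rates are not or much less affected, and the 60-minute emergency-medication and ventilation endpoints are at least partly blinded. The correction is worth making because it is cheap and because the protocol gives safety a part in the trial's conclusion.

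**What to change.** 1. **8.1.1:** replace the sentence by a statement that endpoints assessed after unblinding are open-label and that the physician-judged ones may be subject to assessment bias.
2. **8.2.2 and 2.2:** use one wording that counts the listed adverse-event types regardless of attributed relationship, in line with 7.1.3. Relatedness can be reported in addition.
3. **Hyperammonaemia:** report per arm, descriptively, the number of patients tested and the number positive, without a between-arm test.
4. **T60:** in patients with treatment success, do the GCS and the neurological examination before the envelope is opened. The +/- 5 minute window and the 60-minute limit on blinding must be reconciled, because an examination between 60 and 65 minutes cannot satisfy both.

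The clinical rule for ammonia testing is left to the sponsor; only its consequence for the analysis is at issue. The cost is wording in the protocol and analysis plan and one ordering instruction on the T60 sheet. No visits or tests are added.
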